## Abstract

Pressurized Intra-Peritoneal Aerosol Chemotherapy (PIPAC) is a novel laparoscopic intraperitoneal chemotherapy approach offered in selected patients affected by non-resectable peritoneal carcinomatosis. Drugs doses currently established for nebulization are very low: oxaliplatin (OXA) 120 mg/sm, cisplatin (CDDP) 10.5 mg/sm and doxorubicin (DXR) 2.1 mg/sm. A model-based approach for dose-escalation design in a single PIPAC procedure and subsequent dose escalation steps is planned. The starting dose of oxaliplatin is 100 mg/sm with a maximum estimated dose of 300 mg/sm; an escalation with overdose and under-dose control (for probability of toxicity less than 16% in case of under-dosing and probability of toxicity greater than 33% in case of overdosing) will be further applied. Cisplatin is used in association with doxorubicin: A two-dimensional dose-finding design is applied on the basis of the estimated dose limiting toxicity (DLT) at all combinations. The starting doses are 15 mg/sm for cisplatin and 3 mg/sm for doxorubicin. Safety is assessed according to Common Terminology Criteria for Adverse Events (CTCAE version 4.03). Secondary endpoints include radiological response according to Response Evaluation Criteria in Solid Tumor (version 1.1) and pharmacokinetic analyses. This phase I study can provide the scientific basis to maximize the optimal dose of cisplatin, doxorubicin and oxaliplatin applied as PIPAC.

## 1. Introduction

Peritoneal carcinomatosis (PC) is both a consequence of different primary tumors, synchronous or metachronous, and the clinical presentation of primitive peritoneal neoplasms. Despite significant recent advances in the management of peritoneal carcinomatosis, this diagnosis still is linked frequently to a poor prognosis. The unfavorable outcome is often accompanied by clinical symptoms that dramatically impact on quality of life and represent a real challenge for the managing health care provider.

Curative approach is, unluckily, reserved to a small minority of patients amenable to combined procedures based on cytoreductive surgery and locoregional treatments. The majority of patients is still nowadays treated by palliative approach.

### 1.1. The Failure of Systemic Treatment

The treatment of PC by palliative systemic chemotherapy (sCT) is still, nowadays, often the standard of care. Some cheering improvement in survival are recorded in PC from colonic cancer in which median survival for non-surgical amenable patients raised from six to 24 months by novel drugs agents, as FolfOX/FolfIRI ± bevacizumab [1]. In other PC, such as from gastric cancer, results are not so encouraging: literature reported median overall survival ranging from 4 to 13 months [2,3]. In ovarian cancer, intravenous chemotherapy with platinum compounds, taxanes, anthracyclines, gemcitabine, topotecan and trabectedin in various combinations and sequences are the mainstay of recurrence treatment. These regimens achieve median overall survival rates after the first, second, third, fourth and fifth relapse of 17.6 (95% CI 16.4–18.6), 11.3 (10.4–12.9), 8.9 (7.8–9.9), 6.2 (5.1–7.7) and 5.0 (3.8–10.4) months, respectively [4]. It is remarkable that the intraperitoneal availability of drugs by sCT is low; consequentially, the systemic treatment is often inefficient in bulky disease. Furthermore, the cumulative toxicity of intravenous repeated chemotherapeutic regimens is responsible for progressive decrease of patients’ compliance to therapy.

### 1.2. The Failure of the Intraperitoneal Chemotherapy

Intraperitoneal chemotherapy (IPC) has the potential to improve drug delivery to the tumor with generally accepted systemic side effects [5]. The rationale of this approach is represented by the possibility to consider the peritoneal cavity as a “pharmacologic sanctuary”, due to the presence of the peritoneal-plasma barrier that allows a high drug concentration in the abdominal cavity associated to minimal leakage towards systemic circulation. IPC is reported to be effective but is still burdened by pharmacological limitation, such as low homogeneity in drug distribution in the abdominal cavity [6] and technical problems like the high complication rate related to the intraperitoneal catheter (infections, obstruction, bleeding, dislocation): only 40% of patients are able to complete the expected chemotherapy cycles [7,8]. Furthermore, the poor drug penetration into peritoneal bulky disease (and adhesions-entrapped tumor nodules) in intraperitoneal administration is responsible for mediocre results if IPC is not preceded by optimal cytoreductive surgery [9].

### 1.3. PIPAC as a Promising Intraperitoneal Chemotherapy Delivery Technique

PIPAC takes advantage of the physical properties of gas and pressure avoiding the pharmacokinetic limitations of IPC [10]: under-pressure application and drug micronization enhance drugs uptake, peritoneal distribution and penetration depth [11,12,13].

Based on animal experimental data, PIPAC has been tested in patients with recurrent peritoneal carcinomatosis: It has been administered alone or after systemic fluorouracil [13,14,15]. Concomitant systemic treatment is possible with most used regimens, considering no systemic chemotherapy for two weeks before and one week after PIPAC procedure.

Two intraperitoneal regimens are used for PIPAC procedures: cisplatin in combination with doxorubicin and oxaliplatin as monotherapy. At least three PIPAC procedures are done at six- to eight-week intervals, but treatment can be pursued depending on disease response and patient tolerance.

So far, the dosages of these drugs have been set at approximately 20% of the dose used in HIPEC. Only one phase 1 study increased the doses of cisplatin and doxorubicin applied as PIPAC, setting them to a dosage still too low—10.5 mg/sm and 2.1 mg/sm, respectively [16]. Similarly, the oxaliplatin dose used for PIPAC has recently been the subject of a dose escalation study reporting that the recommended phase 2 dose should be 120 mg/sm [17].

The feasibility, safety and tolerance of repeated PIPAC treatment are confirmed by retrospective and prospective studies. Limited hepatic and renal toxicity are reported, associated to acceptable local toxicity: nausea and diffuse abdominal pain are the most complained complications. No acute or cumulative renal, gastrointestinal and hepatic toxicity are described [18,19,20]. Furthermore, surgical complications are rare. Whereas no mortality is observed in prospective trials, the mortality in retrospective studies is 2.7% [21].

At least, PIPAC has been shown to be safe regarding occupational health aspects such as operation theatre air contamination with aerosol chemotherapy particles [22].

Considering the efficacy of the procedure, not only retrospective studies, but also phase 2 trials described PIPAC as treatment able to induce regression of peritoneal nodules. Clinical response is reported in 62–88% of patients with ovarian cancer, in 50–91% of patients with gastric cancer, in 71–86% of colorectal cancer and 67–75% of peritoneal mesothelioma [21]. Moreover, in patients with advanced peritoneal carcinomatosis, PIPAC has been able to improve quality of life by up to 89% [23].

On the basis of the cited literature, this phase 1 study aims to determine the dose-related safety profile and tolerability of PIPAC with cisplatin, doxorubicin and oxaliplatin by assessment of dose-limiting toxicities and adverse events.

## 2. Materials and Methods

This is a prospective, single center, open-label, non-randomized, two-arm study.

The trial was originally designed in 2015 as a single arm study with repeated dose targeting patients not amenable to standard systemic chemotherapy. This approach significantly compromised the progress of the study since the majority of patients presented general clinical conditions suitable for a systemic treatment. The protocol was, therefore, modified, through an amendment, by creating two study arms:-Cohort A: patients receiving standard systemic chemotherapy cycles in association with PIPAC.-Cohort B: patients ineligible to receive standard systemic chemotherapy who will be treated using the PIPAC procedure alone. A dose escalation design was planned for this arm.

Ethics approval was obtained according to the guidelines of the Declaration of Helsinki and approved by the Ethics Committee of Candiolo Cancer Institute, FPO—IRCCS (EudraCT number 2015–000866-72 version 3.0—4 February 2018) and by the Italian drug agency (AIFA—Agenzia Italiana del FArmaco—5 April 2018); the trial is registered on ClinicalTrials.gov, number NCT02604784.

### 2.1. PIPAC Administration

PIPAC procedure is performed as previously described [24]. Briefly, an open access with a midline 5–6 cm incision is performed and a single-port platform (QuadPort+ Olympus) is positioned according to our original technique (Figure 1). A 12 mmHg CO2 pneumoperitoneum is inflated. Ascites is removed if present and the amount documented. Video documentation is started; PC extent is evaluated according to the Peritoneal Cancer Index (PCI) and multiple peritoneal biopsies are taken for histological examination and baseline tissue drug concentration detection. A nebulizer (Capnopen^®^, Capnomed, Villingendorf, Germany) is connected to a high-pressure injector and inserted into the peritoneal cavity; the tightness of the abdomen is documented with a CO_2_ zero-flow. The camera and the nebulizer are maintained in position by a self-retaining retractor (Thompson). The pressurized aerosol containing cisplatin and doxorubicin or oxaliplatin at the respective dose according to the dose escalating design is applied through the nebulizer. The flow rate is set at 30 mL/min and the maximal upstream pressure is 200 PSI. The injection is remote-controlled in order to avoid occupational exposure. The capnoperitoneum is then maintained for 30 min at 37 °C. At the end, the aerosol is exsufflated through two sequential micro-particle filters into the air-waste system of the hospital. Single-port platform is removed; no abdominal drain tube is applied. Nasogastric tube and urinary catheter are removed at the end of the operation.

### 2.2. Study Population

Eligible patients should present peritoneal mesothelioma, primary peritoneal tumor or unresectable peritoneal metastasis from ovarian, gastric, intestinal and appendiceal cancer. Suitability and eligibility of the patient have to be validated by a multidisciplinary team.

### 2.3. Inclusion Criteria

Patients eligible for recruitment must meet all of the following criteria:-Unresectable peritoneal metastasis on peritoneal cytology/histology;-Age between 18 and 80 years;-Eastern Cooperative Oncology Group (ECOG) performance status ≤2;-Adequate liver function [AST/SGOT and/or ALT/SGPT ≤2.5 × ULN (upper limit of the normal range) or ≤5 × ULN if liver metastases are present, serum bilirubin ≤1.5 × ULN];-Adequate renal function (serum creatinine ≤ 1.5 × ULN or creatinine clearance >50 mL/min);-Cardiac and pulmonary function preserved;-Adequate bone marrow function [absolute neutrophil count (ANC) ≥ 1.5 × 109/L, hemoglobin (Hb) ≥9 g/dL, platelets (PLT) ≥100 × 109/L];-Total recovery or a CTCAE grade ≤1 from all adverse clinical events of previous chemotherapy, including surgery and radiotherapy, except for alopecia;-No chemotherapy/major surgery in the last four weeks prior to the PIPAC procedure;-Written informed consent signed.

### 2.4. Exclusion Criteria

Any of the following is considered an exclusion criterion:-Extra abdominal metastatic disease (with the exception of isolated pleural carcinomatosis);-Bowel obstruction;-History of allergic reactions to cisplatin/doxorubicin/oxaliplatin or their derivatives;-Severe renal failure, myelosuppression, severe hepatic failure, severe heart failure, recent myocardial infarction, severe arrhythmia;-Immunosuppressed patients, undergoing immunosuppressive therapy;-Previous treatment with reaching the maximum cumulative dose of doxorubicin, daunorubicin, epirubicin, idarubicin and/or other anthracyclines and anthracenedions;-Pregnancy;-Patients of both sexes with reproductive potential who refuse to use an adequate method of contraception;-Major surgery or systemic chemotherapy less than four weeks prior to PIPAC procedure.

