Local drug administration limits systemic toxicities thanks to the possibility to consider the peritoneum as a sanctuary in which the peritoneal layer acts as barrier; with cisplatin 100 mg/sm administered via HIPEC, the maximum drug concentration detected in plasma is 1.71 µg/mL [35].

Platinum based intraperitoneal chemotherapy have dose-dependent efficacy [36]: higher intraperitoneal doses result in higher intratumoral concentrations with a consequent higher efficacy. Moreover, the combination of CDDP and DXR appears to be one of the most effective available regimens with acceptable local-regional toxicity [37]. A dose escalation study is, therefore, essential to evaluate cisplatin, doxorubicin and oxaliplatin pharmacokinetics and relative tissue concentrations.

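### Minor safety point: the printed anthracycline exclusion looks only at previous treatment and does not add the trial's own doxorubicin dose

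*Protocol article*

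**What the plan says.** Section 2.4 of the protocol article lists as an exclusion "Previous treatment with reaching the maximum cumulative dose of doxorubicin, daunorubicin, epirubicin, idarubicin and/or other anthracyclines and anthracenedions". The value of the maximum is not printed.

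Other criteria bear on the same risk:

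- Section 2.2: "Suitability and eligibility of the patient have to be validated by a multidisciplinary team".
- Section 2.3: "Cardiac and pulmonary function preserved", and "Total recovery or a CTCAE grade ≤1 from all adverse clinical events of previous chemotherapy".
- Section 2.4: exclusion for "severe heart failure, recent myocardial infarction, severe arrhythmia".

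On dosing, Section 2.6 assigns cisplatin with doxorubicin to ovarian, gastric and primary peritoneal disease. Table 1 gives seven doxorubicin levels: 3, 6, 10, 13, 18, 23 and 30 mg/sm. Section 2.5 has the procedure done once, and Section 2.6 rules out raising the dose within a patient. Section 2.6 sets a maximum of 42 patients, stated with the combination design.

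**The concern.** By writing this exclusion the protocol accepts that lifetime anthracycline exposure has a ceiling that matters for its patients. The test it sets stops one step early: it asks whether the ceiling has already been reached, not whether the dose about to be given would cross it. Some previous exposure is plausible, because Section 1.1 names anthracyclines among the drugs used for recurrent ovarian cancer, and ovarian patients receive the doxorubicin combination.

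At stake is the safety of an individual patient close to the limit. For that patient, protection rests on case-by-case judgement and not on a rule. The dose-limiting toxicity model, the 25% target and the choice of recommended dose are not in question.

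**Working it through.** The plan gives no figure to reproduce here, so the check compares two rules.

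**Inputs**

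- P: previous cumulative anthracycline dose. M: the maximum, not printed. The remaining margin is h = M − P.
- d: assigned doxorubicin dose, 3, 6, 10, 13, 18, 23 or 30 mg/sm (Table 1).
- f: share of the intraperitoneal dose that counts toward M. The document does not give it, so it is an assumption with range 0 to 1.
- Number of procedures: 1 (Section 2.5).

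**Rules compared**

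- Printed rule: exclude if P ≥ M, that is, if h ≤ 0.
- Rule that counts the trial dose: exclude if P + f·d > M, that is, if h < f·d.
- Patients admitted by the first but not by the second: 0 < h < f·d. The gap has width f·d whatever M is, so the missing value of M does not affect it.
- Nominal overshoot for such a patient: f·d − h, which is always below f·d.

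**Upper bound on the overshoot (mg/sm)**

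| Level | d | f = 1 | f = 0.5 | f = 0.1 | f = 0 |
|---|---|---|---|---|---|
| 1 | 3 | 3 | 1.5 | 0.3 | none |
| 2 | 6 | 6 | 3 | 0.6 | none |
| 3 | 10 | 10 | 5 | 1.0 | none |
| 4 | 13 | 13 | 6.5 | 1.3 | none |
| 5 | 18 | 18 | 9 | 1.8 | none |
| 6 | 23 | 23 | 11.5 | 2.3 | none |
| 7 | 30 | 30 | 15 | 3.0 | none |

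**Example, h = 12 mg/sm.** The printed rule admits this patient at every level.

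- f = 1: within the limit at levels 1 to 3. Over it by 13 − 12 = 1, 18 − 12 = 6, 23 − 12 = 11 and 30 − 12 = 18 mg/sm at levels 4 to 7.
- f = 0.5: over it only at level 7, by 15 − 12 = 3 mg/sm.
- f = 0.1: within it at every level, since the largest counted dose is 3 mg/sm.

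**Do the other criteria close the gap?** The cardiac criteria and the recovery criterion test the patient's present condition. Team validation is discretionary and has no dose rule attached. A patient with sound cardiac function, no residual toxicity and a margin of 12 mg/sm meets all the printed criteria on this point.

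**The case against.** The strongest reply is that this is a journal article. Its criteria are short phrases without thresholds or conversion rules, and how exposure is counted may be spelled out in the full protocol. That stands as a limit on the point, which concerns the criterion as printed. It does not remove the point: the criterion is present with its own test, and that test refers to previous treatment. The English is awkward, but no plain reading brings in the trial dose.

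A second reply is that little drug is expected to reach the circulation. Section 1.2 expects "high drug concentration in the abdominal cavity associated to minimal leakage towards systemic circulation", and the Discussion says "Local drug administration limits systemic toxicities". With one dose, team validation and cardiac criteria as well, the practical risk is probably small. This is granted. Still, plasma pharmacokinetics by this route is a secondary endpoint (Section 2.5), so exposure at these doses is something the trial has yet to measure.

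A third reply is that, without M, nobody can say whether 3 to 30 mg/sm is a material excess. That is correct, and it is why the point is graded minor.

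Three stronger readings are tempting but not supported:

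- A reader might set the trial levels against the doses the Abstract gives as established, "cisplatin (CDDP) 10.5 mg/sm and doxorubicin (DXR) 2.1 mg/sm", and infer that escalation brings patients near the limit. That comparison shows how far the trial escalates. It says nothing about closeness to a cumulative maximum.
- A reader might infer that patients will in fact be taken past the limit. The document gives no data on previous exposure.
- A reader might multiply the dose by several procedures, since Section 1.3 describes repeated PIPAC. That is background practice; the endpoint in Section 2.5 concerns a single procedure.

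**Conclusion.** The point holds as a minor safety gap in a printed criterion. Followed exactly, the rule admits a cisplatin-doxorubicin patient whom the assigned dose would nominally carry past a maximum that the protocol itself invokes. The excess is below f·d: under 3 to under 30 mg/sm across the levels at full counting, and nil if none of the dose counts. The 30 mg/sm bound applies only if escalation reaches level 7. At most 42 patients are planned for the combination; the number falling in the gap is unknown and probably small.

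The conclusion rests on the printed wording, on one procedure per patient, and on an assumed f. It does not depend on M. No effect on the escalation design follows from it.

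**What to change.** Add one sentence to the exclusion for patients assigned to cisplatin-doxorubicin: exclude if previous cumulative anthracycline dose plus the doxorubicin dose of the assigned level would exceed the maximum. Count the intraperitoneal dose in full as a conservative convention. One check at dose assignment is enough, because each patient has one procedure and no within-patient escalation.

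The change has two costs:

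- A few heavily pretreated patients become ineligible, some perhaps needlessly. Full counting bars everyone with h < d, although only those with h < f·d would nominally pass the limit. At level 7 with f = 0.1, patients with a margin from 3 up to 30 mg/sm would be barred without need.
- The check depends on dose level, so these patients drop out mainly at the upper levels: a 12 mg/sm margin is accepted at levels 1 to 3 and refused at levels 4 to 7. Pretreatment may then differ slightly along the dose axis on which toxicity is modelled. Record previous cumulative anthracycline dose for every combination patient so that this can be described by level.

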### 2.5. Study Objective

The primary endpoint of the study is to determine the incidence of dose-limiting toxicity of PIPAC with cisplatin, doxorubicin or oxaliplatin (according to the primary pathology) performed once in patients with peritoneal carcinomatosis. Toxicity will be graded using the National Cancer Institute (NCI) Common Terminology Criteria for Adverse Events (CTCAE) version 4.03.

Secondary endpoints will be: pharmacokinetics of cisplatin, doxorubicin and oxaliplatin as pressurized aerosol by the intraperitoneal route; evaluation of the clinical tumor response based on RECIST criteria (version 1.1) after PIPAC.

### 2.6. Statistical Design

Cisplatin and doxorubicin will be used in patients with peritoneal carcinomatosis of ovarian and gastric origin and in primary tumors of the peritoneum. A dose escalation model based on a two-agents combination design published by Riviere is adopted [25]. It is an extension of the Continual Reassessment Method in case of two-dimensional dose-escalation, which identifies the MTD of the combination of cisplatin and doxorubicin based on the probability of dose limit toxicity (DLT) of each combination of the two agents.

An empirical logistic model in a Bayesian framework is adopted. The model of the probability of toxicity at a given dose combination is defined as following:*logit*(*π*(*d*_1*j*_,*d*_2*k*_*α*,*β*_1_,*β*_2_,*β*_3_) = *α* + *β*_1_*d*_1,*j*_ + *β*_2_*d*_2,*k*_ + *β*_3_*d*_1,*j*_*d*_2,*k*_(1)
where *β*_1_ represents the toxicity effect of agent 1 (cisplatin), *β*_2_ of agent 2 (doxorubicin), and *β*_3_ is the interaction effect potentially due to the combination of the agents.

For parameters α and *β*_3_, a vague normal prior distribution centered at 0 to indicate that a priori either positive or negative values are favored, letting the observed number of patients with toxicity driving the posteriori distribution. For parameters (*β*_1_, *β*_2_), an exponential distribution with mean 1 is chosen, based on the consideration that (*β*_1_, *β*_2_) should numerically be in a neighborhood of 1.

The working model is defined by dose levels *d*_1*,j*_ for cisplatin and *d**_2,k_* for doxorubicin, which have been identified on the basis of a modified Fibonacci series.

The first cohort of participants will be treated with cisplatin 15 mg/sm body surface in 150 mL NaCl 0.9% and doxorubicin 3 mg/sm (cohort 1); the following cohort will receive CDDP 30 mg/sm and DXR 6 mg/sm (cohort 2) and the third cohort CDDP 50 mg/sm and DXR 10 mg/sm (cohort 3). Dose escalation will be continued by the protocol according to the probability model up to a maximum of CDDP 100 mg/sm (that is the dose currently used in HIPEC procedure) and DXR 30 mg/sm.

The different dose increases will be adopted as reported in Table 1.

The recommended doses of both agents are those of the dose level combination associated with a probability of DLT closes to the DLT probability target at 25%. An escalation with overdose and under-dose control (for probability of toxicity less than 16% in case of under-dosing; and probability of toxicity greater than 33% in case of overdosing) is further applied. No skipping dose is allowed, nor intra-patient dose escalation.

As a stopping rule, the maximum number of 42 patients is considered.

Oxaliplatin will be used in patients presenting peritoneal carcinomatosis of intestinal origin.

An extension of the Continual Reassessment Method based on a two-parameter probability model proposed by Neuenschwander will be used to identify the recommended dose of oxaliplatin [26].

The first cohort of patients will be treated with oxaliplatin 100 mg/sm body surface in 150 dextrose solution 5% (cohort 1); the following cohort will receive oxaliplatin 135 mg/sm (cohort 2) and 155 mg/sm for the third one (cohort 3).

After each cohort is assessed, a probability of toxicity, given the data observed (i.e., the number of patients who experienced toxicity), is computed on the basis of the following 2-parameters logistic regression model
*logit*(*π*(*d***_j_*;*α*,*β*) = *log**α* + *β* × *d***_j_*, *α*,*β* > 0(2)
where the parameters (*α*, *β*), which are positive valued, ensure a monotonically increasing dose-toxicity relationship; *d***_j_* is a dose standardized to a reference dose, so that log *α* can be interpreted as the log-odds of toxicity when *d**_*i*_ is the reference dose.

Parameters (*α*, *β*) will be calibrated to reflect information about toxicities, corresponding to assuming a toxicity probability of oxaliplatin at the maximum dose of 460 mg equal to 25% and a toxicity probability at the starting dose of 120 mg equal to 10. Calibration of the parameters will be carried out according to the approach proposed in Thall [27], assuming a zero a priori correlation.

An escalation with overdose and under-dose control (for probability of toxicity less than 16% in case of under-dosing; and probability of toxicity greater than 33% in case of overdosing) is further applied. No skipping dose is allowed, nor intra-patient dose escalation.

The dose escalation design of oxaliplatin is presented in Table 2.

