## Figures and Tables

**Figure 1 ijerph-18-05656-f001:**
[figure not shown]
Schematic of single-port PIPAC set-up. The nebulizer connected to a standard injector and a laparoscope are inserted through a Quadport+ platform.

**Table 1 ijerph-18-05656-t001:** Cisplatin and doxorubicin dose escalation design.

Level	Cisplatin (CDDP)	Doxorubicin (DXR)
1	15 mg/sm	3 mg/sm
2	30 mg/sm	6 mg/sm
3	50 mg/sm	10 mg/sm
4	67 mg/sm	13 mg/sm
5	88 mg/sm	18 mg/sm
6	93 mg/sm	23 mg/sm
7	100 mg/sm	30 mg/sm

**Table 2 ijerph-18-05656-t002:** Oxaliplatin dose escalation design.

Level	Oxaliplatin (OXA)
1	100 mg/sm
2	135 mg/sm
3	155 mg/sm
4	180 mg/sm
5	200 mg/sm
6	235 mg/sm
7	270 mg/sm
8	300 mg/sm

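### The cisplatin-doxorubicin part is called a two-dimensional search over all combinations, but the doses set out form one ordered ladder of seven pairs, on which the two drug effects separate only weakly and interim overdose probabilities rest on unstated prior and coding choices

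*Protocol article*

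**What the plan says.** The Abstract states that "A two-dimensional dose-finding design is applied on the basis of the estimated dose limiting toxicity (DLT) at all combinations". Section 2.6 (Statistical Design) describes an extension of the continual reassessment method that "identifies the MTD of the combination of cisplatin and doxorubicin based on the probability of dose limit toxicity (DLT) of each combination". Its equation (1) is a logistic model with four parameters and separate dose indices j and k. Beta1 is the cisplatin effect, beta2 the doxorubicin effect, and beta3 "is the interaction effect potentially due to the combination of the agents". Alpha and beta3 get "a vague normal prior distribution centered at 0", with no variance given. For beta1 and beta2, "an exponential distribution with mean 1 is chosen".

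The doses are set out differently. Cohorts 1 and 2 receive 15/3 and 30/6 mg/sm (cisplatin/doxorubicin), and "the third cohort CDDP 50 mg/sm and DXR 10 mg/sm (cohort 3"). Section 2.6 then says "The different dose increases will be adopted as reported in Table 1". Table 1, captioned "Cisplatin and doxorubicin dose escalation design", has a single Level column and seven rows: 15/3, 30/6, 50/10, 67/13, 88/18, 93/23 and 100/30. The target DLT probability is 25%, with underdosing below 16% and overdosing above 33%. The maximum is 42 patients, and no dose may be skipped.

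**The concern.** In a two-dimensional search, one agent can be raised while the other is held, and the toxicity order of some combinations is unknown beforehand. None of the pairs in Table 1 has that property. Each has more of both drugs than the one before, so the pairs form a single ordered sequence. The article therefore states two designs that do not match, and equation (1) is built for the one that Table 1 does not show.

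Two things are at stake. A reader would expect the trial to report on combinations that it never gives. And the model that steers escalation has four parameters, of which the ladder informs some poorly, so the priors carry weight in early decisions. Section 2.6 requires positive parameters for oxaliplatin so that toxicity rises with dose. The combination model has no such guarantee along a ladder that is just as ordered.

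**Working it through.** **Inputs from the article:** the seven pairs of Table 1, equation (1), Exp(1) priors for beta1 and beta2 (SD 1), mean-zero normal priors for alpha and beta3, the 33% overdose limit and the maximum of 42.

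**Assumed, because the article does not give them:** normal variance 10 or 100; doses coded as dose/maximum or log(dose/maximum); 6 patients per level (42/7 = 6); the DLT counts named below.

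**1. Shape of the ladder.** The cisplatin:doxorubicin ratios are 5.00, 5.00, 5.00, 5.15, 4.89, 4.04 and 3.33. The correlation of the two doses is 0.953 over all levels and 0.999 over levels 1 to 5. Crossing the levels would give 7 × 7 = 49 cells; Table 1 names 7.

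**2. Separation of the drug effects, levels 1 to 3.** With cisplatin = 5 × doxorubicin and dose/maximum coding, d1 = 5·DXR/100 and d2 = DXR/30, so d1 = 1.5·d2. Equation (1) becomes

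logit π = α + (1.5β1 + β2)·d2 + 1.5β3·d2².

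Only the sum 1.5β1 + β2 enters. The design matrix has rank 3 of 4. Three pairs could not give more than rank 3 in any case; the 5:1 ratio places the loss in the split between β1 and β2. On log dose, d1 = d2 + log 1.5, so d1 and d2 are again exactly linearly related and the rank is again 3.

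**3. After level 3.** Rank is 4 from level 4 on, but the conditioning is poor. The condition number on dose/maximum is 500 over levels 1 to 4, 172 over levels 1 to 5 and 64 over all seven (full grid: 15.8). Variance inflation factors over all seven levels are 16, 198 and 134 for d1, d2 and their product (full grid: 3.7, 5.3 and 8.1).

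**4. Posterior with all seven levels filled** (6 per level, DLTs 0,0,1,1,2,2,3, variance 10):

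| Parameter | Prior SD | Posterior SD, dose/max | Posterior SD, log dose |
|---|---|---|---|
| β1 | 1.00 | 0.97 | 0.88 |
| β2 | 1.00 | 0.97 | 0.70 |
| β3 | 3.16 | 1.47 | 1.31 |

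Beta1 and beta2 stay close to their priors, more so on one coding than on the other. Beta3 is clearly updated.

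**5. Posterior when escalation to level 4 is decided** (6 per level on levels 1 to 3, DLTs 0,0,1). Probability that level 4 exceeds 33%:

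| Coding | Variance 10 | Variance 100 |
|---|---|---|
| dose/max | 9% | 30% |
| log dose | 44% | 75% |

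On dose/maximum the 95% interval for DLT at level 4 widens from 1–49% to 0–85%. All four settings fit the article's description, and the data are the same in each.

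**6. Monotonicity.** Because beta3 may be negative, toxicity falls somewhere along the ladder in 38% to 48% of prior draws over the four settings. After the three cohorts of step 5 the share is 24% to 33% on dose/maximum, but only about 2% to 4% on log dose.

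**The case against.** The best reply is that the design needs less than the concern supposes. The recommended dose depends on the DLT probability at a combination, not on splitting that probability between drugs. The slopes are working parameters, and section 2.5 lists no drug-specific or interaction estimate among the endpoints. Proper priors give a proper posterior at every stage. This stands. A reader might infer that the model cannot be identified at all, or that beta3 merely returns its prior. Neither is so: the matrix has full rank from level 4, and the SD of beta3 falls from 3.16 to 1.47.

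A reader might also infer that the extra parameters blur all seven level estimates. With the full data of step 4, a two-parameter logistic model on cisplatin dose (assumed normal intercept with variance 10, exponential slope with mean 2) gives posterior SDs of DLT probability of 0.065, 0.089, 0.100 and 0.117 at levels 4 to 7. The four-parameter model gives 0.066, 0.081, 0.100 and 0.151. Only level 7 is clearly worse, and on log dose the differences are about 0.005 or less. The inflation factor of 134 for the product term also owes much to uncentred coding; centring the doses brings it to 6.0.

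Finally, Table 1 might list marginal levels, with a fixed diagonal start and model-guided moves afterwards. The separate indices and the statement that escalation continues according to the model leave room for this, and the rules could sit in the full protocol. Then 49 cells for 42 patients (42/49 = 0.86 per cell) is no defect in itself, since a parametric model pools across cells. But the article's own statements still need reconciling: a single Level column, increases adopted as tabulated, and a step from 15/3 to 30/6 that raises both drugs together under a no-skipping rule not defined per agent.

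**Conclusion.** The mismatch between the stated design and the stated doses is in the text and holds without any assumption. On the fixed-pair reading, which the single Level column and the first three cohorts favour, the search is one-dimensional and DLT at all combinations cannot be what the trial studies.

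The statistical consequence is narrower than failure of the model. The split between beta1 and beta2 is not estimable from the data through level 3 under either coding tried, and afterwards rests largely on the Exp(1) priors. Beta3 is partly learned, and DLT probabilities at the tested pairs are estimable once all levels have data. The practical weakness lies in the interim decisions: with identical assumed data, the overdose probability at level 4 runs from 9% to 75% across prior variances and codings that the article leaves open, and rising toxicity along the ladder is not assured.

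These figures rest on the assumed 6 patients per level, DLT counts, variances and codings; others would move them. The documents do not support the inference that the recommended dose will be wrong, and no operating characteristics were available to show it.

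**What to change.** State whether Table 1 lists fixed pairs or the marginal levels of each drug.

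- **If fixed pairs:** describe a one-dimensional escalation over the seven ordered pairs. Use a model that is monotone along them, for example the two-parameter logistic form already adopted for oxaliplatin, with prior DLT probabilities given for the seven levels. Drop the interaction term and the two-dimensional and all-combinations claims in the Abstract and section 2.6.
- **If a grid:** list the admissible combinations, and reconcile Table 1, the path of cohorts 1 to 3 and the no-skipping rule with it, saying how skipping is judged when two agents change.

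In either case, state the normal prior variance and the dose coding.

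The cost is a change to model specification and wording. Under the fixed-pair option the trial gives up separate drug and interaction estimates, which the ladder hardly supports.
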